## **2.2. Secondary endpoint (Progression-free Survival) analysis**

### **2.2.1. Primary analysis methods**

Estimates, including progression-free survival curves, median progression-free survival, and time-point progression-free survival, will be performed using Kaplan-Meier method. Greenwood formulas will be used to obtain 95% confidence intervals. Log-rank test is used for comparison between arms.

### **2.2.2. Analysis methods using statistical models.**

Hazard ratios and their 95% confidence intervals for treatment effects are estimated using unstratified Cox proportional hazards models.

### **2.2.3. Method of subgroup analysis**

To investigate the interaction between treatment effect and the subpopulation, subgroup analyses will be conducted in an exploratory manner with respect to the following factors. Because these analyses are not adequately powered and do not adjust for multiplicity, the results of each subgroup analysis should be interpreted as exploratory.

Factors planned for subgroup analysis:

- PS0/1
- Age 65 years or older/<
- Gender (male/female)
- Primary organ (gastrointestinal tract/hepatobiliary pancreas)
- Organ of origin (esophagus/stomach/small intestine/large intestine/pancreas/biliary tract/liver NEC (liver primary or liver metastasis of unknown primary))
- Organ of origin (pancreas/non-pancreas)
- Extent of extension of the primary lesion (locally advanced/distant metastasis or recurrence)
- Extent of extension of the primary lesion (locally advanced/distant metastasis/recurrence)
- Prior radical resection of the primary lesion (none/present)
- Pathological diagnosis was biopsy/resection specimen
- Grade 3 tumour with morphologically similar features of NETs but Grade 3 proliferative activity/morphologically more atypical (previously classified as poorly differentiated endocrine carcinoma) on histopathology with central pathology
- Histopathological examination by central pathological diagnosis, including Small cell carcinoma/Large cell carcinoma /
- Histopathologically diagnosed by central pathology, Ki67 50% or higher/less than 50%

#### **2.2.4. Method of supplementary analysis**

To evaluate the robustness of the analysis results for PFS, the following sensitivity analyses will be performed if necessary.

- Hazard ratios and their confidence intervals for treatment effects between arms using a stratified Cox proportional hazards model for all enrolled patients.
- Hazard ratios and their confidence intervals for treatment effects between arms using a unstratified Cox proportional hazards models including clinical background factors differentially distributed between arms as covariates (\* analysis population is all enrolled patients).
- Hazard ratios and their confidence intervals for treatment effects between arms using unstratified Cox proportional hazards model for all eligible patients.
- Hazard ratios and their confidence intervals for treatment effects between arms using the same stratified Cox proportional hazards model as in the primary analysis (\* analysis population is patients eligible for central pathology review).

#### **2.2.5. Handling of missing data**

No imputations will be made for missing data. We censor patients who did not progress following criteria in Section 11.3.2 in the protocol. Note that we describe how to address a problem when there exists missing data which may seriously affect the analysis results.

### **2.3. Secondary endpoint (response rate) analysis**

#### **2.3.1. Primary analysis methods**

Response rate is a proportion of patients among all eligible patients with measurable disease who are categorized into CR or PR according to the criteria in the Section 11.1.10 in the protocol. Fisher's exact test will be used to compare response rates between groups, and the exact confidence intervals will be constructed using Clopper and Pearson method.

#### **2.3.2. Analysis methods using statistical models**

Odds ratios and their confidence intervals will be constructed using logistic regression models if necessary.

#### **2.3.3. Method of subgroup analysis**

To investigate the interaction between treatment effect and the subpopulation, subgroup analyses will be conducted in an exploratory manner with respect to the following factors. Because these analyses are not adequately powered and do not adjust for multiplicity, the results of each subgroup analysis should be interpreted as exploratory.

Factors planned for subgroup analysis

- PS0/1
- Age 65 years or older/<

- Gender (male/female)
- Primary organ (gastrointestinal tract/hepatobiliary pancreas)
- Organ of origin (esophagus/stomach/small intestine/large intestine/pancreas/biliary tract/liver NEC (liver primary or liver metastasis of unknown primary))
- Organ of origin (pancreas/non-pancreas)
- Extent of extension of the primary lesion (locally advanced/distant metastasis or recurrence)
- Extent of extension of the primary lesion (locally advanced/distant metastasis/recurrence)
- Prior radical resection of the primary lesion (none/present)
- Pathological diagnosis was biopsy/resection specimen
- Grade 3 tumour with morphologically similar features of NETs but Grade 3 proliferative activity/morphologically more atypical (previously classified as poorly differentiated endocrine carcinoma) on histopathology with central pathology
- Histopathological examination by central pathological diagnosis, including Small cell carcinoma/Large cell carcinoma /
- Histopathologically diagnosed by central pathology, Ki67 50% or higher/less than 50%

#### **2.3.4. Method of supplementary analysis**

To confirm the robustness of the primary analysis results, the following sensitivity analyses will be performed if necessary.

- ORR and the 95% confidence interval among all enrolled patients with measurable disease.
- ORR and the 95% confidence interval among all patients who are eligible for centrally pathological review and with measurable disease.

#### **2.3.5. Handling of missing data**

No imputations will be made for missing data. Patients whose best response are NE will be categorized as non-responders and will not be excluded from the analysis.

### **3. Safety analysis**

Among secondary endpoints, the safety endpoints are the incidence of adverse events and the incidence of serious adverse events, which are in principle the items of periodical monitoring (see Section 14.1 in the protocol)

#### **3.1. Proportion of patients with adverse events**

The proportion is calculated to evaluate differences in toxicity among the two groups. Frequency of adverse events marking the worst grade in CTCAE v4.0-JCOG that occurred during the entire course of therapy will be calculated (by group) using the number of all treated patients as a denominator. If necessary, exact confidence intervals will be calculated and Fisher's exact test will be used for group comparisons.

#### **3.2. Proportion of patients with serious adverse events**

Grade 4 non-hematologic adverse events, early deaths, and treatment-related deaths are defined as serious adverse events which are reported in semi-annual Monitoring Report with patient registry numbers and details.

In addition, the incidence of Grade 4 non-hematologic adverse events, early deaths, and treatment-related deaths will be calculated for all treated patients when comparing efficacy analyses between arms.

Exact confidence intervals for the proportion is calculated.

Neither of these is judged based on statistical tests, but comparisons are made between arms using Fisher's exact test, as appropriate.

### **4. Other analyses**

#### **4.1. Dose intensity of cisplatin**

Summary statistics (minimum, percentiles [25%/50%/75%], maximum, mean, and SD) of dose intensity (D.I.) regarding cisplatin will be calculated. Analysis population is all treated patients. The aim is to evaluate the treatment compliance of cisplatin.

- Actual D.I. (mg/m^2/week) = (total amount of cisplatin) /BSA/ (treatment duration [weeks])
  - BSA = weight0.425 x height0.725 x 0.007184  
(For weight and height, the values calculated in data center at the timing of enrollment are used)
  - Treatment duration (weeks)
    - ✧ For arm A, it is defined as a duration from the initiation date of the first treatment course to the date of 21 days from the initiation date of the last treatment course.
    - ✧ For arm B, it is defined as a duration from the initiation date of the first treatment course to the date of 28 days from the initiation date of the last treatment course.

## 5. Interim analysis

### 5.1. Purpose of the interim analysis

One interim analysis will be conducted to determine if the primary objective of the study has been achieved during the study period. Interim analysis will be conducted to determine if it is reasonable to continue enrollment during enrollment. If the primary objective of the study is determined to be achieved, the study will be discontinued and the study results will be published promptly at the conference and in the article.

### 5.2. Timing for interim analysis

Interim analysis will be conducted using data from the initial periodic monitoring that will be queried after the time enrollment of half of the planned enrollment was obtained. Based on the information in the periodic monitoring report, the group will submit the presence or absence of changes in clinical hypotheses and, if any, details of changes to the Data and Safety Monitoring Committee by the time of the interim analysis.

During interim analysis, patient accrual will not be halted in principle. If the study progressed as expected, the expected number of events at the time of the interim analysis is expected to be 44 if the interim analysis is conducted at 3 years after the start of enrollment.

### 5.3. Multiplicity adjustment methods in interim analyses

Interim analysis will be conducted by the JCOG Data Center. To control the study-wise type-I error rate at 10%, the multiplicity of the interim and final analyses is adjusted using Lan & DeMets's alpha spending functions, and the calculated statistical significance level is used for testing primary endpoint between arms. As alpha spending functions, we use O'Brien & Fleming type.

### 5.4. Decision Criteria in the interim analysis

Decision criteria based on the results of the interim analysis is following.

- If superiority of arm B over arm A (or vice versa) is demonstrated based on a criterion that the two-sided p-value calculated from stratified log-rank test is below the significance level calculated from the method detailed in Section 5.3, then the study is to be discontinued due to an efficacy.
- Otherwise, the study is to be discontinued.

Futility stop is also considered from various aspects. As a reference, the following is calculated.

- Predictive probability for primary endpoint (based on Spiegelhalter et al. (1992)) that will be calculated based on a Bayesian predictive distribution of hazard ratio on the final analysis. To calculate the following predictive probabilities, log-rank score statistic calculated from the stratified log-rank test for overall survival (in the primary analysis) is used.
  - Predictive probability that the superiority of arm B over arm A (or vice versa) will be demonstrated on the final analysis (at the time of information time=1).
  - Predictive probability that point estimate of hazard ratio for arm A will be greater than one on the final analysis (at the time of information time=1).
  - Predictive probability that point estimate of hazard ratio for arm B will be greater than one on the final analysis (at the time of information time=1).
- Conditional power for primary endpoint (based on Halperin et al. (1982)). To calculate the following conditional power, log-rank score statistic calculated from the stratified log-rank test for overall survival (in the primary analysis) is used.

- Conditional power given the observed interim analysis data that the trial would reject the null hypothesis on the final analysis assuming the true hazard ratio for arm A after 1st interim analysis would be one (the null hypothesis for the primary analysis)
- Conditional power given the observed interim analysis data that the trial would reject the null hypothesis on the final analysis assuming the true hazard ratio for arm B after 1st interim analysis would be one (the null hypothesis for the primary analysis)
- Conditional power given the observed interim analysis data that the trial would reject the null hypothesis on the final analysis assuming the true hazard ratio for arm A after 1st interim analysis would be 0.67 (the expected hazard ratio for overall survival)
- Conditional power given the observed interim analysis data that the trial would reject the null hypothesis on the final analysis assuming the true hazard ratio for arm B after 1st interim analysis would be 0.67 (the expected hazard ratio for overall survival)

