### **1.2. Multiplicity Adjustment**

For a reason that our primary interest is whether either of two arms is superior to the other, two-sided test is used. The study-wise significance level is set at two-sided 10%. In the primary analysis, two-sided 90% confidence intervals corresponding to a two-sided 10% significance level will be calculated, and in the other analyses, two-sided 95% confidence intervals will be calculated for descriptive purposes.

Significance levels and corresponding confidence coefficients used to test the primary hypotheses are based on the multiplicity adjustment associated with the interim analysis.

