## **5.5. Reporting and review of the results**

The results of the interim analysis will be submitted to the Data and Safety Monitoring Committee by the Data Center as an Interim Analysis Report and reviewed for the acceptability of continuation of the study and for publication of the results. The Data and Safety Monitoring Committee considers whether to continue the study at the meeting and recommends whether to continue the study and whether to inform the results to principal physician or group chair based on the results of the review.

Members of the Data and Safety Monitoring Committee of the relevant groups are not included in the review. Unless the results of the interim analysis make recommendations for discontinuation of the study from the Data and Safety Monitoring Committee, the research representative, research office, participating institution researchers, group representatives, and group secretaries of the study will not be able to know the results of the interim analysis until the final follow-up is completed.

When the Interim Analysis Report has been reviewed by the Data and Safety Monitoring Committee to recommend termination or change of all or part of the study, the principle investigator and group chair review the recommendations and decide whether to discontinue or change some of the study.

If the study is discontinued or part of the study is changed, the principal investigator and group chair shall submit in written form a request to the Data and Safety Monitoring Committee for permission to discontinue the study or a request to revise the protocol. Following approval by the Data and Safety Monitoring Committee, the principal investigator may discontinue the study or change part of the study.

The Study Chair and Group Chair can disagree with the recommendations of the Data and Safety Monitoring Committee, but if they fail to coordinate their opinions with the Data and Safety Monitoring Committee, they will ultimately follow the instructions of JCOG Chair.

If the study is terminated, the subsequent follow-up period will be 1 years from the date of last registration.

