## 7. Planned accrual, accrual period, and follow-up periods

As described in "Section 2.4.2. in the protocol. Based on the background presented in Clinical Hypothesis and Rationale for Number of Enrollment", we assume a median survival of 8 and 12 months (HR=0.67) for inferior and superior treatment groups. Total of 63 patients per group and 126 patients in both groups (114 events required) will be required using the method of Schoenfeld and Richter. The above calculation assumes 6 years of enrollment, 1 year of follow-up,  $\alpha = 10\%$  (two-sided), and 70% power. The required number of patients and events are listed in table below when median survival time of arm A is different to the expectation.

Table: Number of Analyses Required (Number of Events Required)

| Median Survival
(mo) | Power    |          |          |          |
|-------------------------|----------|----------|----------|----------|
|                         | 65%      | 70%      | 75%      | 80%      |
| 7.0 vs. 10.5            | 108(100) | 124(114) | 142(131) | 162(150) |
| 8.0 vs. 12.0            | 112(100) | 126(114) | 144(131) | 166(150) |
| 9.0 vs. 13.5            | 114(100) | 130(114) | 148(131) | 170(150) |

※ Number of required events in parentheses

Based on these, the following will be established in view of some cases of loss to follow-up.

Planned enrollment: 70 patients in each group and 140 patients in both groups

Enrollment period: 6 years, follow-up period: 1 year after completion of enrollment

Consider sample size recalculation (SSR) if the prognosis is obviously better than assumed, or if 70 or more patients are enrolled within first 2.5 years. The SSR needs reconsideration of clinically meaningful differences in a blinded fashion and needs to be performed prior to the conduct of the primary analysis.

<Additions in protocol ver. 1.1>

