The registration pace after the enrollment start was smooth and exceeded the plan, and 70 cases were enrolled in October, 2016, when 2 years and 2 months passed from the enrollment start, which met the above-mentioned criteria for SSR. SSR with an aim of raising power to 80% was accepted at the meeting of the Hepatobiliary and Pancreatic Group on October 29, 2016, the group meeting of the Esophageal Cancer Group on November 19, 2016, and the group meeting of the Gastric Cancer Group on January 7, 2017. Therefore, the required number of enrollment was changed to 170. In addition, the "1-year analysis period" was added to the study period, and the following changes were made.

Planned enrollment: 85 patients in each group and 170 patients in both groups

Enrollment period: 6 years;

Follow-up period: 1 year after completion of enrollment;

Analysis period: 1 year;

Total study period: 8 years

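### SAP Section 5.4 words the interim decision rule so that both branches discontinue the study; the rest of the SAP requires a continue outcome, and the wording is probably a translation slip

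*SAP*

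**What the plan says.** SAP Section 5.4 sets out the decision criteria in two bullets. The first covers a stratified log-rank p-value below the level derived in Section 5.3: "then the study is to be discontinued due to an efficacy". The second covers everything else: "Otherwise, the study is to be discontinued". Directly below, the section says that a futility stop is also considered. It lists predictive probabilities and conditional power, all of which refer to the final analysis.

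Other parts of the SAP treat continuation as a live outcome:

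- Section 2.1.1 makes the final analysis the primary analysis unless the study ends at the interim.
- Section 5.1 describes the purpose: "Interim analysis will be conducted to determine if it is reasonable to continue enrollment during enrollment". It ties discontinuation to the primary objective having been achieved.
- Section 5.5 has the committee recommend whether the study goes on. It keeps the results from the investigators until the end of follow-up, with one exception: "Unless the results of the interim analysis make recommendations for discontinuation of the study from the Data and Safety Monitoring Committee".
- Section 6 plans a final analysis one year after accrual ends.
- The supplemental note for the final analysis (2021/6) spends all the remaining alpha at information time 1.

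**The concern.** The two bullets of Section 5.4 between them cover every possible interim result, and both lead to the same action. A decision rule whose outcome does not depend on the data decides nothing. No other sentence in Section 5.4 restores a continue branch. The futility paragraph makes the conflict plainer, because conditional power at the final analysis has no use if failing to cross the boundary already ends the study.

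This section links the alpha spending to an action. A reader who takes it at face value would find either a trial planned to end at its first look or a trial that did not follow its own rule. The first conflicts with the group-sequential design. The second bears on confidence in the confirmatory result.

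**Working it through.** **Inputs, all from the SAP**

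- Overall level (Section 1.2): "The study-wise significance level is set at two-sided 10" per cent.
- Spending function (Section 5.3): "As alpha spending functions, we use O'Brien & Fleming type".
- Effect (Section 7): "we assume a median survival of 8 and 12 months (HR=0.67) for inferior and superior treatment groups".
- Power after recalculation (Section 7): "SSR with an aim of raising power to 80% was accepted". The table there gives 150 events at 80% power. Allocation is 85 per group.
- Interim (supplemental note 2017/9): 55 events, information time t = 55/150 = 0.3667, two-sided level 0.0024178, boundary ±3.0334.
- Final (supplemental note 2021/6): 151 events observed, two-sided level 0.0992020, boundary ±1.6487.

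**Step 1: reproduce the stated boundaries.** With 0.05 spent on each side, the O'Brien-Fleming-type spend per side is 2 × [1 − Φ(z(0.975)/√t)].

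- z(0.975)/√t = 1.9600/0.6055 = 3.237.
- Doubling the per-side spend gives a two-sided level of 0.0024178, so |Z| = 3.0334. Both match the SAP.
- The final boundary comes from the bivariate normal distribution with correlation √t = 0.6055, solved for an overall two-sided level of 0.10. The result is 1.6487, a nominal level of 0.09920. Both match the SAP.
- With the stated pair of boundaries, the overall level is 0.1000.

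The final boundary is defined only for trials that pass the interim without stopping, so the SAP's own calculation assumes continuation.

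**Step 2: reproduce the event target.** Schoenfeld's formula is 4 × (z(0.95) + z(0.80))² / (ln 1.5)². This gives 4 × (1.6449 + 0.8416)² / 0.1644 = 150.4, against 150 in the Section 7 table.

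**Step 3: how often the second branch applies.**

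- Under the null: 1 − 0.0024178 = 99.76%.
- At the design effect (hazard ratio 8/12), the expected value of Z at 55 events is √(55/4) × ln 1.5 = 3.708 × 0.4055 = 1.503. The chance of crossing is Φ(1.503 − 3.033) = Φ(−1.530) = 6.3%, so 93.7% fall in the second branch.
- At the rounded hazard ratio of 0.67, the chance of crossing is 6.1%.

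**Step 4: power under the two readings of the second bullet.**

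| Reading | Hazard ratio 8/12 | Hazard ratio 0.67 |
|---|---|---|
| Discontinue (as worded), interim is the primary analysis | 6.3% | 6.1% |
| Continue to 150 events | 79.8% | 79.0% |

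Only the second reading agrees with the planned 80%. Under the first, 0.0024 of the 0.10 alpha is ever used.

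**Step 5: sensitivity to the interim event count.** Section 5.2 forecast 44 events at the interim. With 44 events the chance of crossing at hazard ratio 8/12 would be 1.8% against a target of 150 events, or 5.5% against the 114 events required before recalculation. The conclusion does not depend on the 55 events that occurred.

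**The case against.** The strongest reply is that this is one wrong word in a translation. The SAP opens by saying that it is an abridged translation from Japanese, and *discontinued* for *continued* is an easy slip. The intended meaning can be recovered from Sections 2.1.1, 5.1, 5.5 and 6 and from the futility paragraph. The trial acted on that meaning: the 2021/6 note reports 170 patients and 151 events at the final analysis. This stands, and it limits the point to the wording of the rule. It does not remove the point, because the original is not at hand and the English text states the rule wrongly.

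Three stronger readings might be inferred, and the SAP does not support them.

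- *Followed as written, the trial must always stop.* Section 5.5 leaves the recommendation to the committee and the decision to the principal investigator and group chair, with further committee approval before any stop. Section 5.4 does not carry itself out.
- *The committee worked from this wording.* Nothing shows that it used the English abridgement.
- *The remaining 95 of 150 events would never have been seen.* Section 5.5 continues follow-up for one year after the last registration if the study is terminated, so further deaths would be recorded. The loss of power in Step 4 remains, because Section 5.5 also makes the interim analysis the primary analysis in that case.

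**Conclusion.** The point holds as an error in the stated decision rule. The criteria in Section 5.4 have no continue outcome and contradict Sections 2.1.1, 5.1, 5.5 and 6, the futility quantities in the same section, and the alpha kept for the final analysis.

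Taken literally, the defective branch would govern about 94% of trials at the design effect and 99.76% under the null, and power would be about 6% instead of about 80%. These figures assume proportional hazards, 1:1 allocation, the normal approximation to the log-rank statistic without allowance for stratification, and an interim at 55 of 150 events.

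They describe the rule as worded, not what happened. The study continued, both boundaries reproduce, and no reported significance level or analysis is affected. A translation slip is the likely cause but cannot be confirmed from this text. The apparent departure from the stopping rule is therefore not evidence of misconduct of the trial.

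**What to change.** First compare the second bullet of Section 5.4 with the original-language SAP and with the protocol. If the original says *continued*, correct the translation and note the correction. If it says *discontinued*, the governing plan itself needs the correction, with a dated explanation that the trial was run on the other reading.

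In either case the bullet should say, in substance: if the boundary is not crossed, the study continues to the final analysis, unless the Data and Safety Monitoring Committee recommends stopping for futility after considering the quantities listed below. That wording agrees with Sections 2.1.1, 5.1, 5.5 and 6.

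The cost is one sentence and one document check. No boundary, sample size or analysis needs to be recalculated.
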